### Study interventions

Participants will be randomly allocated to Elusion™ e-cigarettes supplied by PGM International with nicotine cartridges (16 mg), to nicotine patch (Habitrol^®^ 21 mg patch, distributed in NZ by Novartis Consumer Health Australasia Pty. Ltd.) or to e-cigarettes with placebo (0 mg) cartridges in a ratio of 4:4:1. Participants issued with an e-cigarette will be instructed to charge the batteries daily for reliable operation using a USB charger that comes with the device, alone or in combination (if needed) with an adaptor plug.

Participants in the 16 mg nicotine e-cigarette treatment arm will be sent (by courier) a free e-cigarette and sufficient nicotine cartridges (16 mg/ml) to last for four to five weeks. Participants will be instructed to use the device *ad libitum* one week before their quit day to familiarise themselves with its operation and on their designated quit day will stop smoking tobacco cigarettes and instead use the e-cigarette exclusively for the next 12 weeks.

Those in the placebo e-cigarette arm will be sent a free e-cigarette and cartridges containing 0 mg nicotine. Participants will use the device in the same manner as described above for the nicotine e-cigarette treatment group. The cartridges will be labelled in such a way that participants cannot detect if they contain nicotine.

In the nicotine patch arm, participants will be sent (by post) vouchers to be exchanged for a minimal dispensing fee (NZ$3) at any community pharmacy for 21 mg (full strength, 24 hour) nicotine patches. All participants will receive a $5 voucher to be used at any community pharmacy on any product they wish, to cover their out of pocket expenses. Participants will use the nicotine patch daily for one week before their quit day to familiarise themselves with its use. On their designated quit day they will stop smoking and use nicotine patches daily for the next 12 weeks. This dosing regimen is consistent with what is now regarded as standard treatment in NZ and many other countries. The 21 mg strength patch is likely to be sufficient nicotine replacement for the majority of smokers recruited into the trial.

All participants will be referred to the NZ toll-free smoking cessation support helpline, Quitline (http://www.quit.org.nz), for a standardised cessation behavioural support programme delivered by trained advisors, with a minimum of one follow-up support telephone call over 8–12 weeks. If people do not want to receive this support, they will be able to access other Quitline support services such as ‘Txt2Quit’ (a mobile phone based support service), ‘QuitCoach’ (an internet based support service), and the ‘Quitter’s community’ (an internet based blogging forum) (Figure 1).

**Figure 1 F1:**
[figure not shown]
Trial schema showing key design features and timelines.

### Baseline assessments

Following randomisation the following additional baseline data will be collected from each participant: *Demographic information*: socio-economic position (based on education level attained); *Smoking history*: age when started smoking, number of cigarettes smoked per day, number of years as regular smoker, type of cigarettes smoked per day (e.g. roll-your-own or factory-made), usual pouch/pack size (and how long a pack lasts), number of previous unsuccessful attempts to give up in past 12 months and the method used including past history of any e-cigarette use; *Other smoking related information:* self-rated chances of quitting, other household members smoking at home or in cars with participant; *Use of any other smoking cessation treatments*: use of NRT or non-nicotine methods of cessation; *Physical signs and symptoms associated with withdrawal*: measured using the Autonomy Over Smoking Scale (AUTOS) [25]; *Chances of quitting: self-rated chances of quitting success measured on a scale of 1–5*; *Concomitant medication*: information about types of medication currently used; *Behavioural factors in smoking dependence*: measured using the Glover-Nilsson Smoking Behavioural Questionnaire (GH-SBQ) [26]. A total GN-SBQ score is calculated by summing all 11 items (range 0 to 4) with a score < 12 indicating a mild level of behavioural dependence, 12–22 a moderate level of behavioural dependence, 23–33 a strong level of behavioural dependence and >33 a very strong level of behavioural dependence.

### Primary outcome

The primary outcome for the trial is the proportion of participants who maintain sustained (continuous) abstinence from smoking for six months after their quit day. Abstinence is defined using the Russell Standard (i.e. intention to treat analysis, smoking five cigarettes in all [from the Quit date], plus biochemical verification of self-reported abstinence via exhaled carbon monoxide [CO] measurement, using the Bedfont Microplus device, of less than 10 parts per million) [27].

### Secondary outcomes

The following secondary outcome measures are being assessed in all participants at quit day and at one, three and six months after the Quit date: *Continuous abstinence* (as defined, at one and three months); *Seven-day point prevalence*: defined as the proportion of participants who self-report having smoked no cigarettes (not even a puff) in the past 7 days; *Use of cigarettes*: smoking at any time-point will trigger the following assessments - number of cigarettes smoked per day; proportion of participants who have significantly reduced daily smoking (defined as reducing consumption by at least 25% in terms of numbers of cigarettes per day or weight of loose tobacco per day); *Participants’ treatment compliance:* number of patches or e-cigarette cartridges used per day; early stopping and reasons why; *Perception of the product*: participant views on using e-cigarettes or patches as a smoking cessation aid (including what they liked and disliked about it and whether they would recommend the treatment to another smoker); *Use of any other smoking cessation treatments*; *Physical signs and symptoms associated with withdrawal*; *Pre-quitting stage of addiction and smoking latency: using a scale for latency to smoking developed by Ursprung* et al. [28]*. Adverse events*: Information regarding any adverse events and whether they are related to treatment.

### Sample size

A sample size of 657 people (292 in both nicotine-cigarette and nicotine patch groups and 73 in the placebo e-cigarette group) will provide 80% power at a two-sided p = 0.05 to detect an absolute difference of 10% in smoking abstinence rates between the nicotine e-cigarette and patch groups, and a difference of 15% between the nicotine and placebo e-cigarette groups. This assumes quit rates of 15% in the placebo e-cigarette group and 20% in the nicotine patch group (based on meta-analyses of NRT trials by Fiore et al. [29] and our own trials of nicotine patch [30]). This sample size allows for analysis of consistency of effects for pre-specified subgroups (e.g. Maori, non-Maori) to be assessed. Based on our previous experience we estimate recruitment will take approximately 12–15 months [31].

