**Methods/design:**

*Design:* Parallel group, 3-arm, randomised controlled trial. *Participants:* People aged ≥18 years resident in Auckland, New Zealand (NZ) who want to quit smoking. *Intervention:* Stratified blocked randomisation to allocate participants to either Elusion™ e-cigarettes with nicotine cartridges (16 mg) or with placebo cartridges (i.e. no nicotine), or to nicotine patch (21 mg) alone. Participants randomised to the e-cigarette groups will be told to use them *ad libitum* for one week before and 12 weeks after quit day, while participants randomised to patches will be told to use them daily for the same period. All participants will be offered behavioural support to quit from the NZ Quitline. *Primary* o*utcome:* Biochemically verified (exhaled carbon monoxide) continuous abstinence at six months after quit day. *Sample size:* 657 people (292 in both the nicotine e-cigarette and nicotine patch groups and 73 in the placebo e-cigarettes group) will provide 80% power at *p* = 0.05 to detect an absolute difference of 10% in abstinence between the nicotine e-cigarette and nicotine patch groups, and 15% between the nicotine and placebo e-cigarette groups.

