### Randomisation, allocation concealment and sequence generation

Callers will be told about the trial and asked if they would like to take part by a research assistant. If interested, they will be asked for basic demographic data (age, sex and ethnicity) and checked to see if they meet the trial inclusion criteria. Those who provide further details about their level of nicotine dependence (determined by the Fagerström Test for Nicotine Dependence [FTND] questionnaire [24]) will be randomised by a central computer programme to one of the three study groups using stratified block randomisation with block sizes of nine. The randomisation sequence will be prepared in advance by the study statistician (VP) but will be concealed from research assistants enrolling participants. Participants will be assigned to the 16 mg e-cigarette and nicotine patch groups in a ratio of 1:1 (290 in each) and to the nicotine e-cigarette and placebo e-cigarette groups in a ratio of 4:1 (73 in the latter arm). Three stratification factors will be used: ethnicity (Māori, Pacific, non-Māori non-Pacific), sex (male/female) and level of nicotine dependence (> 5 or ≤ 5 on the FTND [24]).

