### Statistical analysis

A senior biostatistician determined the sample size and wrote the statistical analysis plan agreed upon by all members of the Steering Committee specifying *a priori* all analyses to be undertaken. All statistical analyses will be performed using SAS version 9.3 (SAS Institute Inc. Cary, North Carolina, US) and R version 2.11.1 software (http://www.r-project.org). All regression analyses will be conducted for the following two comparisons: 16 mg e-cigarette versus nicotine patch groups; and 16 mg e-cigarette versus 0 mg e-cigarette groups.

No interim analyses will be undertaken. All tests of significance will be two-tailed. The primary analyses will be carried out on an intention to treat (ITT) basis. The ITT population will comprise all randomised participants regardless of whether they actually satisfied the entry criteria, the treatment was actually received and they subsequent withdrew or deviated from the protocol. The numbers discontinuing treatment prematurely for any reason will be summarised by treatment group and by reasons for discontinuation. The incidence of all suspected serious adverse treatment reactions will be summarised by treatment group in line with the CONSORT 2010 recommendations [32]. Simple incidence rates, relative and absolute risks, numbers needed to treat will be calculated for all binary variables, and the treatment groups will be compared using chi-squared tests with multiple logistic regression analysis adjusting for other variables as appropriate. The distribution of all continuous outcomes will be assessed for normality and skewed data will be subjected to an appropriate transformation before analysis. The change from baseline in physical signs and symptoms associated with withdrawal (AUTOS) [25] and number of cigarettes smoked per day will be analysed using repeated measures models adjusting for baseline value. The proportion of participants who have significantly reduced their daily smoking level (defined as reducing consumption by at least 50% in terms of numbers of cigarettes per day) will be calculated, and in users of loose tobacco, the size of pouch/package currently bought and number of days taken to smoke its contents measured. Finally, the number of other quit attempts in the last six months will be calculated.

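### The planned chi-squared test has about 77% power, not 80%, for nicotine versus placebo e-cigarettes, and the two larger arms are given as both 290 and 292 (minor)

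*Protocol article*

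**What the plan says.** The Sample size section sets 657 participants: 292 on nicotine e-cigarettes, 292 on patch and 73 on placebo e-cigarettes. This number "will provide 80% power at a two-sided p = 0.05" to detect 10 points against patch "and a difference of 15% between the nicotine and placebo e-cigarette groups". The assumed quit rates are 20% on patch and 15% on placebo. The Abstract makes the same claim, including "15% between the nicotine and placebo e-cigarette groups". Neither place names the formula used.

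For binary outcomes, the Statistical analysis section says "the treatment groups will be compared using chi-squared tests", together with multiple logistic regression.

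The Randomisation section describes the nicotine e-cigarette and "nicotine patch groups in a ratio of 1:1 (290 in each"), and nicotine to placebo e-cigarettes "in a ratio of 4:1 (73 in the latter arm"). It gives a block size of nine. The Study interventions section gives the overall ratio as 4:4:1.

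**The concern.** One power figure is given for two comparisons of different shape, one allocated 1:1 and the other 4:1. Under unequal allocation the common approximations to the power of a two-proportion test diverge, so a figure that is right for the first comparison need not be right for the second.

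The placebo comparison is the second listed trial hypothesis. The Discussion gives it as the reason for the third arm: to separate the effect of nicotine from that of the substitute behaviour. It rests on only 73 placebo participants. A null result there would be read against a stated type II error of 20%, when the planned test carries about 23%.

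The two arm sizes leave the recruitment target ambiguous by four participants.

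**Working it through.** **Inputs.** From the Sample size section: two-sided alpha 0.05 (z = 1.96); arms of 292, 292 and 73; 20% on patch; 15% on placebo; differences of 10 and 15 points. The nicotine e-cigarette rate is not written out, but both comparisons imply 30% (20 + 10 and 15 + 15). The test, from the Statistical analysis section, is chi-squared; no continuity correction is mentioned. No allowance for dropout is stated and none is applied.

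**Formula.** Power = Φ[(d − 1.96 × SE0) / SE1]. SE0 uses the pooled rate p̄, weighted by arm size as in Pearson's statistic: SE0 = √[p̄(1 − p̄)(1/n1 + 1/n2)]. SE1 uses the two separate rates: SE1 = √[p1(1 − p1)/n1 + p2(1 − p2)/n2].

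**Patch comparison (292 v 292, 30% v 20%).**
- p̄ = 0.25
- SE0 = √(0.1875 × 2/292) = 0.0358
- SE1 = √[(0.21 + 0.16)/292] = 0.0356
- Power = Φ[(0.10 − 0.0702)/0.0356] = 79.8%; full binomial enumeration gives 80.1%

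The stated 80% reproduces.

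**Placebo comparison (292 v 73, 30% v 15%).**
- p̄ = (292 × 0.30 + 73 × 0.15)/365 = 0.27
- SE0 = √[0.27 × 0.73 × (1/292 + 1/73)] = 0.0581
- SE1 = √(0.21/292 + 0.1275/73) = 0.0497
- Power = Φ[(0.15 − 0.1139)/0.0497] = 76.7%; full binomial enumeration of the uncorrected Pearson test gives 77.4%

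The enumeration involves no approximation. The test's type I error at common rates of 20% to 30% is 4.9% to 5.0%, so the shortfall does not come from a conservative test.

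**Routes that come near 80% for the placebo comparison.**

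| Method | Power at 292 v 73 | Placebo n for 80% at 4:1 |
|---|---|---|
| Fleiss, simple average p̄ = (0.30 + 0.15)/2 = 0.225 | 80.6% | 72 |
| Arcsine | 79.4% | 75 |
| Likelihood-ratio test, exact enumeration | 79.2% | not computed |
| Fleiss, weighted p̄ = 0.27 | 76.7% | 79 |

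The first row follows from SE0 = √[0.225 × 0.775 × (1/292 + 1/73)] = 0.0546, so Φ[(0.15 − 0.1071)/0.0497] = 80.6%. For arcsine, 2·asin√0.30 − 2·asin√0.15 = 0.364, and 0.364 × √(292 × 73/365) − 1.96 = 0.82, so Φ(0.82) = 79.4%.

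**Difference detectable with 80% power.** Holding placebo at 15%, the weighted formula gives 79.3% at a nicotine rate of 30.5% and 80.5% at 30.75%. Interpolation puts 80% at about 30.6%, a difference of about 15.6 points.

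**Arm sizes.**
- 292 + 292 + 73 = 657; 292/73 = 4.00; 657/9 = 73 whole blocks
- 290 + 290 + 73 = 653; 290/73 = 3.97

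Using 290 in place of 292 gives 76.6% (exact 77.0%) for placebo and 79.6% (exact 79.9%) for patch, a change of less than half a point.

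**The case against.** The strongest reply is that the stated 80% can be reproduced. The arcsine formula respects the 4:1 allocation and gives 79.4%. Fleiss with a simple average gives 80.6% and asks for 72 placebo participants against the 73 planned. The likelihood-ratio test, a natural test for the logistic model that the article also plans, has 79.2%. The article names no power formula, and a condensed article may leave that to a fuller document. The control rates are themselves assumptions, and error in them could outweigh 0.6 of a point.

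Most of this stands. It probably explains where the figure came from, and it keeps the point small. It does not remove it, because the claim is about what the trial will provide, and the test that the article names for comparing groups has about 77% under the article's own assumptions.

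A reader might infer that the sample size was miscalculated, or that the placebo arm must be enlarged. The documents do not support either: the planned numbers agree closely with standard approximations, and the gap is about 3 points. A reader might also quote the lower power of a continuity-corrected or Fisher test. The article plans neither, so such figures are not evidence against it. In the other direction, the fully unpooled formula gives 85.6%, but that is not the chi-squared test.

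On 290 against 292, it is fair to say that the other figures settle which number was meant. The contradiction is still in the text.

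**Conclusion.** The point holds as a minor correction. For nicotine versus placebo e-cigarettes the stated power is about 3 points too high for the uncorrected chi-squared test: 77.4% exact, or 76.7% by the pooled approximation, against 80%. This rests on 292 v 73 participants, 30% v 15% abstinent, two-sided 0.05 and no loss of information from dropout. The patch comparison is correctly stated. The article gives too little to say which approximation produced the 80%, and the overstatement reflects how approximations differ under 4:1 allocation.

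The 290/292 contradiction is certain and does not depend on any formula. It shifts the implied total by four participants and has a negligible effect on power.

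**What to change.** In the Abstract and the Sample size section, give 80% power for the patch comparison. For the placebo comparison, give about 77% at 15 points with the uncorrected chi-squared test, or equivalently 80% at about 15.6 points. Name the method used for the power calculation.

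In the Randomisation section, change 290 to 292 so that it agrees with 657, 4:1, 4:4:1 and blocks of nine.

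The cost is wording only. No participants are added, and the allocation and analysis do not change. The one consequence is a slightly less favourable power statement for the placebo comparison.

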### Withdrawal criteria

Should participants require discontinuation of study treatment for any reason, (such as significant intolerance to the study treatment, any serious clinical adverse event, inter-current illness, pregnancy or other condition that indicates to the principal investigator that continued treatment is not in their best interest) or if they elect to cease taking treatment, follow-up calls and data collection will continue as scheduled as if they were continuing with the randomised treatment. If the participant discontinues treatment due to a serious adverse event, the participant will be followed until the event resolves or there is a return to a clinically acceptable medical status. Participant deaths or serious adverse events within 30 days of discontinuation will be reported to the project co-ordinator.

### Data management

We will capture all study data on a web-based data management system using an Oracle database. Validation rules for each case record form have been pre-specified and include range checks so inaccuracies in data collection can be identified early. A query is raised for values outside the allowed range or if data are missing, and the form amended as soon as a query is resolved.

### Data monitoring

An independent study monitor will perform audits of every randomised participant’s record and ensure that study documentation is up-to-date, record keeping adheres to the study protocol and with regulatory requirements, and handling of the study medication is appropriate.

### Statistical analysis

A senior biostatistician determined the sample size and wrote the statistical analysis plan agreed upon by all members of the Steering Committee specifying *a priori* all analyses to be undertaken. All statistical analyses will be performed using SAS version 9.3 (SAS Institute Inc. Cary, North Carolina, US) and R version 2.11.1 software (http://www.r-project.org). All regression analyses will be conducted for the following two comparisons: 16 mg e-cigarette versus nicotine patch groups; and 16 mg e-cigarette versus 0 mg e-cigarette groups.

No interim analyses will be undertaken. All tests of significance will be two-tailed. The primary analyses will be carried out on an intention to treat (ITT) basis. The ITT population will comprise all randomised participants regardless of whether they actually satisfied the entry criteria, the treatment was actually received and they subsequent withdrew or deviated from the protocol. The numbers discontinuing treatment prematurely for any reason will be summarised by treatment group and by reasons for discontinuation. The incidence of all suspected serious adverse treatment reactions will be summarised by treatment group in line with the CONSORT 2010 recommendations [32]. Simple incidence rates, relative and absolute risks, numbers needed to treat will be calculated for all binary variables, and the treatment groups will be compared using chi-squared tests with multiple logistic regression analysis adjusting for other variables as appropriate. The distribution of all continuous outcomes will be assessed for normality and skewed data will be subjected to an appropriate transformation before analysis. The change from baseline in physical signs and symptoms associated with withdrawal (AUTOS) [25] and number of cigarettes smoked per day will be analysed using repeated measures models adjusting for baseline value. The proportion of participants who have significantly reduced their daily smoking level (defined as reducing consumption by at least 50% in terms of numbers of cigarettes per day) will be calculated, and in users of loose tobacco, the size of pouch/package currently bought and number of days taken to smoke its contents measured. Finally, the number of other quit attempts in the last six months will be calculated.

A per-protocol analysis will be performed for the primary analysis to check the robustness of the results where participants with any major protocol violations such as cross-over treatments, withdrawals and loss to follow-up will be excluded. Secondary analyses will be conducted with overall cessation rates corrected for discordance between reported and biochemically confirmed cessation. The consistency of effects for pre-specified sub-groups will also be assessed using tests for heterogeneity. Time-to-first-lapse will be analysed using Kaplan-Meier curves, the log rank test and Cox proportional hazards regression analysis.

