The trial will report on clinical efficacy and adverse effects over a six month period of observation. This follow-up period is sufficient to determine if smokers are assisted to quit and to see if the use of nicotine e-cigarettes leads to an excess of adverse effects after eight week’s use over and above placebo e-cigarettes or nicotine patch. The results will make a valuable contribution to the Cochrane Systematic Review on electronic cigarettes for smoking cessation and reduction [34].

The study does not address the safety of long-term use of e-cigarettes (beyond 13 weeks). Neither will the study address the role of e-cigarettes as a ‘gateway’ product to tobacco smoking or a trigger to relapse to tobacco smoking. To answer these questions will require other studies using different designs.

Finally, our study will not provide a definitive answer to address all e-cigarette regulation issues. However, should the findings be in favour of nicotine e-cigarettes without additional adverse effects then it will establish a new balance between clinical benefit and harm for three month’s use of e-cigarettes.

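### Chi-squared tests for every binary variable: in the 292 v 73 placebo comparison, an uncorrected test gives too many false signals for very rare outcomes, all of them towards fewer events on nicotine

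*Protocol article*

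**What the plan says.** The protocol article, Statistical analysis, sets one rule for yes/no outcomes: "numbers needed to treat will be calculated for all binary variables, and the treatment groups will be compared using chi-squared tests", followed by logistic regression with adjustment where suitable. It adds: "All tests of significance will be two-tailed". It mentions no exact test, continuity correction or minimum expected count.

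Sample size gives the arm sizes: "A sample size of 657 people (292 in both nicotine-cigarette and nicotine patch groups and 73 in the placebo e-cigarette group". Study interventions gives the allocation as "or to e-cigarettes with placebo (0 mg) cartridges in a ratio of 4:4:1".

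Secondary outcomes includes "Information regarding any adverse events and whether they are related to treatment". The Discussion makes safety a between-arm question: follow-up is held to be long enough "to see if the use of nicotine e-cigarettes leads to an excess of adverse effects" beyond those seen with placebo e-cigarettes or patch. For suspected serious reactions, Statistical analysis promises only a summary by group. No sentence takes adverse events out of the general rule.

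**The concern.** The chi-squared test relies on a large-sample approximation. With four people on nicotine for each one on placebo and very few events, the null distribution is lopsided: a lone event falls on placebo one time in five, yet the approximation treats that as a 1-in-22 result (p = 0.045). Individual adverse event types are the outcomes most likely to be this sparse, and each would be a separate test.

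What is at stake is the trial's comparison of harms between nicotine and placebo e-cigarettes. A false signal from this source always points the same way, towards fewer events on nicotine, and it could rest on a single event.

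**Working it through.** **Inputs.** From the article: 292, 292 and 73 participants; two-sided 5% level; chi-squared for all binary variables. Adverse event rates are not given, so I assume equal true rates in both arms and vary them. I read chi-squared as Pearson without continuity correction.

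**1. The plan's own figures.** The stated differences imply 30% abstinence on nicotine e-cigarettes (20% + 10%, and 15% + 15%). With h = 2|arcsin√p₁ − arcsin√p₂| and (1.960 + 0.842)² = 7.849, the size is 2 × 7.849/h² = 291.7 per large arm for 20% v 30%. For 15% v 30% at 4:1 it is 1.25 × 7.849/h² = 74.1 on placebo. The article's 292 and 73 (= 292/4) are reproduced closely enough to use.

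**2. One event.** For 1/73 v 0/292:

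χ² = 365 × (1 × 292 − 0 × 72)² / (73 × 292 × 1 × 364) = 365 × 4/364 = 4.01, p = 0.045.

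Fisher's exact p is 73/365 = 0.20, mid-p is 0.10 and the Yates-corrected p is 0.45. The mirror table, 0/73 v 1/292, gives Pearson p = 0.62. The pattern is not limited to one event: 2/73 v 1/292 gives Pearson 0.042, Fisher 0.10. Using the 290 per large arm given under Randomisation gives 0.046 for the single event. A three-group test on 1/73, 0/292, 0/292 gives χ² = 8.01 on 2 df, p = 0.018, so that reading does not avoid the problem.

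**3. Given the number of events.** If an event type occurs exactly once and treatment has no effect, Pearson declares it significant with probability 0.20, always as a placebo excess. With three events in total the probability is 0.103, and with five it is 0.057.

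**4. Over all possible tables.** At a common rate π, type I error is the sum of Bin(a; 73, π) × Bin(b; 292, π) over tables with p < 0.05. The Pearson column also splits it as placebo excess / nicotine excess.

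| True rate | Expected placebo events | Pearson (split) | Fisher | Mid-p |
|---|---|---|---|---|
| 0.1% | 0.07 | 5.3% (5.3/0) | 0.2% | 0.2% |
| 0.2% | 0.15 | 7.9% (7.9/0) | 0.6% | 0.6% |
| 0.4% | 0.29 | 9.2% (9.2/0) | 1.2% | 1.3% |
| 0.5% | 0.36 | 9.0% (9.0/0) | 1.4% | 1.6% |
| 1% | 0.73 | 6.5% (6.5/0) | 1.8% | 2.6% |
| 1.4% | 1.02 | 4.9% (4.9/0) | 1.8% | 3.1% |
| 2% | 1.46 | 3.8% (3.8/0.02) | 2.1% | 3.5% |
| 3% | 2.19 | 3.8% (3.4/0.4) | 2.9% | 4.1% |
| 5% | 3.65 | 4.8% (3.5/1.4) | 3.6% | 4.8% |
| 6.8% | 4.96 | 4.8% (3.2/1.6) | 3.6% | 4.9% |
| 10% | 7.30 | 5.0% (3.1/1.9) | 3.8% | 4.9% |

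Pearson crosses 5% between 1.3% (5.2%) and 1.4% (4.9%). At 0.05% it is 3.1%, because usually no event occurs at all.

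**5. The harm direction.** With no placebo events, the smallest nicotine count giving p < 0.05 is 15 under Pearson (p = 0.048), and also 15 under Fisher (0.049) and mid-p (0.032).

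**6. The patch comparison.** For 1/292 v 0/292, Pearson p = 0.32. Type I error at true rates of 0.3% to 20% is 1.0% to 5.0%.

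**The case against.** The article says that a separate statistical analysis plan fixes all analyses in advance. That plan is not shown, and a switch to an exact test or a continuity correction for sparse tables is routine content there. Either would remove the single-event signal. Testing each adverse event type is also an inference from the words on all binary variables, since the only sentence specific to safety promises a summary of serious reactions. This limits how firmly the point can be put. It does not dispose of it: the article states a rule for every binary variable, safety is a named comparison, and the rule as published gives a wrong error rate for part of what it covers.

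A reader might infer more than the figures support:

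- *The test fails wherever an expected count is below 5, that is, at rates below 5/73 = 6.8%.* It does not. At the rates checked from 1.4% to 6.8%, total Pearson error stays below 5%.
- *Chi-squared is why 15 nicotine events against none are needed to show harm.* Fisher needs exactly 15 too. With 14 or fewer events in total, no nicotine excess can reach p < 0.05 under either test. That follows from the 4:1 allocation.
- *The logistic regression will break down when an arm has no events.* The article commits to adjusted models only where appropriate, so it does not require one there.
- *The trial will declare nicotine e-cigarettes safer than placebo on one event.* Nothing in the article says that it would draw this conclusion from a single test.

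**Conclusion.** The point holds in a limited form. Read as uncorrected Pearson, the stated test is anti-conservative in the nicotine v placebo e-cigarette comparison for outcomes with a true rate from about 0.1% to 1.3%. Its type I error there reaches 9.2% against a nominal 5%, wholly in the direction of fewer events on nicotine. From about 1.4% upwards the total error is about 5% or less, although at 5% it is still split unevenly between the directions (3.5% v 1.4%).

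The primary outcome, at assumed rates of 15% to 30%, and the patch comparison are unaffected. The conclusion rests on three assumptions: no continuity correction, significance tests applied to individual rare adverse events, and event rates in the range examined. The article settles none of them. The change is worth making because it is cheap and concerns a safety question that the trial sets itself; it does not threaten the main result.

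**What to change.** Amend the sentence in Statistical analysis, or confirm that the analysis plan already does so. Sparse binary outcomes in the placebo comparison, such as rare adverse events, should be compared by Fisher's exact or mid-p test and reported with counts and a score or exact confidence interval for the risk difference. Keep chi-squared for abstinence and other common outcomes. State the trigger for sparse in advance.

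The usual trigger, an expected count below 5, is wider than the problem. With Fisher it would replace a test that holds its level by one running at about 1.8% to 3.6% over rates of 1.4% to 6.8%. Mid-p loses less, at 3.1% to 4.9%.

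The cost is one sentence and no new data. The downside is that exact tests are conservative at very low rates, and Fisher slightly lowers power to see nicotine harm: for 2% on placebo v 8% on nicotine, from 45% with Pearson to 41%. Neither test makes up for the small placebo arm, so the safety conclusion should rest on the interval and not on whether p falls below 0.05.
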